**Note:**

- The above drugs are repeated every 3 weeks.
- Patients that achieved CR and PR could receive for up to one-year treatment using sintilimab combined with chidamide or until disease progression, intolerable toxicity, death, or termination of the study for any reason. Patients with SD and PD withdrew from the study.

#### 5.1.2 Phase II study

**Objective:** To evaluate the short-term objective response rate, long-term efficacy, and safety of sintilimab combined with chidamide in the treatment of refractory and relapsed ENKTCL patients.

**Number of subjects:** 28 patients.

**Administration of study drug:** The Phase II study was conducted according to the RP2D of chidamide from Phase Ib clinical study.

- Chidamine: During the combined treatment, the dose is administered according to the recommended dose of RP2D.
- Sintilimab dose: 200mg (fixed dose)

**Note:**

- The above drugs are repeated every 3 weeks.
- Patients that achieved CR and PR could receive for up to one-year treatment using sintilimab combined with chidamide or until disease progression, intolerable toxicity, death, or termination of the study for any reason. Patients with SD and PD withdrew from the study.
- After 12 months, patients still with CR or PR were allowed to choose to continue or end of treatment or accepted autologous hematopoietic stem cell transplantation (ASCT) as consolidation (Stem cell mobilization, collection, reinfusion, conditioning regimen prior to autologous hematopoietic stem cell transplantation followed the medical routine at each study site).
- If patients choose to continue sintilimab plus chidamide, doses of chidamide reduce to 20mg twice a week and fixed doses of 200mg sintilimab intravenously every 30 days.

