and safety of HDACi in ENKTL are controversial. From November 2016 to February 2018, we enrolled 15 patients with r/r ENKTL treated with three therapeutic dose modes of single-agent chidamide (30mg twice a week; 20mg every other day; 10mg once a day, respectively). ORR was 50.0% (6/12) with CR rate 33.3% (4/12). Three patients got CR in 30mg group; one patient got CR in 10mg group. The median time to response was 5.9 (1.1 to 8.1) weeks. Median follow-up time was 3.7 months (0.8-11.5). Our study results suggested that chidamide was effective as single agent in the treatment of r/r ENKTL.

Recent studies on the role of epigenetics in immune evasion have exposed a key role for epigenetic modulators in augmenting the tumor microenvironment and restoring immune recognition and immunogenicity. Moreover, accumulating evidences have shown the synergism between epigenetic drugs and anti-PD-1 antibody. Recent studies have shown that in combination with epigenetic modulators, such as histone deacetylase inhibitors (HDACi) or DNA methyltransferases (DNMTi), can reverse the resistance or ineffectiveness of immune checkpoint inhibitors, supported by both in vitro and in vivo studies. Therefore, targeted epigenetics maybe a therapeutic strategy to improve the efficacy of immunotherapy in RR-ENKTL.

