### **3. Study Design**

#### **3.1 Overall Study design**

This is a phase Ib/II study including dose exploration, followed by the multi-center, open-label extended study.

The dose exploration of the Phase Ib study, a standard “3+3” design was utilized to identify the maximum tolerated dose (MTD), dose limited toxicities (DLTs) and recommended Phase II dosage (RP2D) of chidamide in combination with sintilimab. Once the MTD, DLT and RP2D of Chidamide is determined, the Phase II study shall begin.

The phase II study is proceeded according to the RP2D of chidamide. Patients that achieved CR and PR could receive for up to one-year treatment, otherwise until disease progression, death, intolerable toxicity, completion of the scheduled treatment cycle, or the investigators' decision to withdraw (whichever occurs first). After 12 months, patients still with CR or PR were allowed to choose to continue or end of treatment or accepted autologous hematopoietic stem cell transplantation (ASCT) as consolidation (Stem cell mobilization, collection, reinfusion, conditioning regimen prior to autologous hematopoietic stem cell transplantation followed the medical routine at each study site). If patients choose to continue sintilimab plus chidamide, doses of chidamide reduce to 20mg twice a week and fixed doses of 200mg sintilimab intravenously every 30 days. Dose interruptions were allowed for treatment-related adverse events until these events resolved to grade 0–1 or to baseline level. Treatment was permanently discontinued for patients who had interruptions of more than 4 weeks. Patients will be visited for end of treatment within 4 weeks after the end of the study. For those whose condition is stable or improved after treatment, progression-free survival (PFS) follow-up will be carried out 8 weeks after the last administration of the study drug, and

continued every 12 weeks thereafter until disease progression, death, withdrawal of informed consent (ICF), receiving other novel treatments, or termination of the entire study (whichever occurs first). At the same time, patients who have developed PD will be followed up for overall survival (OS) every 12 weeks until death, withdrawal of ICF, or the termination of the entire study (whichever occurs first). The survival follow-up is conducted every 8 weeks for patients with disease progression.

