### 3.3 Treatment Period

In phase Ib, patients received oral escalating doses of chidamide (20, 25, 30 mg) twice a week continuous and fixed doses of 200mg sintilimab intravenously over a period of 30–60 min, once every 21 days. If DLTs does not occur, the established dose escalation plan could be proceeded to the next level. If one case of DLT occurs, 3 more subjects should be added to this dose level until there is no new DLT report. If there are more than 2 cases of DLT, the forward dose level of this dose level is defined as MTD. The dose level of Sintilimab is 200 mg (fixed dose) each time and repeated every three weeks. Patients that achieved CR and PR could receive for up to one-year treatment. Patients defined with SD and PD should withdraw from the study.

The phase II study is proceeded according to the RP2D of Chidamide. Patients that achieved CR and PR could receive for up to 12 months treatment, otherwise until disease progression, death, intolerable toxicity, completion of the scheduled treatment cycle, or the investigators' decision to withdraw (whichever occurs first).

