### **5.12 Criteria for discontinuation of research drugs or exit of this trial**

If any of the following occurs, the subject must stop the research drug:

1. Occurrence of treatment-related AEs that meet the discontinuation criteria specified in the study protocol.
2. Disease progression (subjects who meet the criteria for medication after disease progression can continue to be treated until the radiological evaluation confirms the progression and rules out the possibility of false progression).
3. During the study period, subjects receiving any prohibited combined treatments that affect the judgment of safety and efficacy can be required to stop the research drug after determined by the investigator and the sponsor's medical monitor.
4. Any intermittent disease that prevents the subject from continuing to receive research drug treatment.
5. The female subject is pregnant.
6. If the subject or his/her guardian is unwilling to continue the clinical research, he/she can propose to the doctor in charge at any time and discontinue the research drug immediately. According to the Declaration of Helsinki and other applicable laws and regulations, subjects have the right to withdraw from this

study at any time for any reason, and doctors or research centers must not be prejudiced in their future medical care.

7. Subjects who have poor compliance and fail to take medications on time and in amounts, when communication and coordination by the investigator is ineffective, or may cause significant deviations in the test results which cannot be remedied, can be determined to discontinue the research drug by the investigators.
8. Other situations where the investigator considers inappropriate to continue medication. Under any condition, the primary reason for discontinuing the research drug should be recorded in the original medical record. If the subject discontinues the research drug for any reason, for subjects who have received at least one research drug, the investigator shall make every effort to persuade the subject to accept the termination visit, and should continue to follow up those subjects with unresolved AEs.

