## **7.2 Evaluation of efficacy**

The efficacy of the study drug will be determined by the objective tumor evaluation made by the research center based on the RECIL 2017 Response Criteria for Malignant Lymphoma.

Radiological evaluation of tumor is determined by PET/CT, MR or CT with uniformity in evaluation method as well as machine and technical parameters throughout the study period. Unless contraindications, contrast agents should be used. The radiological results are interpreted by researchers or radiologists in each research center. If the tumor evaluation has been performed within 21 days before enrollment with the same method and machine in the same hospital, it can be used as a baseline tumor evaluation. The baseline tumor evaluation should include the nasal cavity, chest, abdomen, pelvis and any other suspected areas. If there are clinical indications, appropriate methods, such as cranial MRI, bone scan can be used to examine any other known or suspected disease sites.

From the day of the first administration, radiological examination will be performed to evaluate the tumor condition every 6 weeks (-7 days) until the completion of 6 cycles of treatment, PD, intolerable toxicity, death, investigator's decision or patient's voluntary withdrawal from the study (whichever occurs first). Repeated every 8 weeks after 6 cycles up to 12 months, or disease progression, intolerable toxicity, death, investigators' decision, or the patient's voluntary withdrawal from the study. Researchers can arrange additional radiological examinations based on the patient's clinical conditions. If the medication is suspended due to AE or other reasons, the tumor evaluation will still be carried out as originally planned. For patients who are suspected of developing PD before the next scheduled tumor evaluation, an unscheduled tumor evaluation should be performed.

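### Phase II has no consistent rule for stable disease: section 5.1.2 withdraws these patients at an unnamed scan, sections 3.1 and 3.3 can be read as keeping them on drug, and follow-up continues elsewhere

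*Protocol*

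**What the plan says.** **Phase II treatment section.** The note in section 5.1.2 states "Patients with SD and PD withdrew from the study". The note for phase Ib in section 5.1.1 has the same sentence. Neither names a scan or a week.

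**Treatment period.** Section 3.3 has one paragraph per phase. The phase Ib paragraph ends with "Patients defined with SD and PD should withdraw from the study". The phase II paragraph has no such sentence and says instead: "Patients that achieved CR and PR could receive for up to 12 months treatment, otherwise until disease progression, death, intolerable toxicity", followed by completion of the scheduled cycles or the investigator's decision.

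**Overall design.** Section 3.1 gives the phase II rule in nearly the same words: "Patients that achieved CR and PR could receive for up to one-year treatment, otherwise until disease progression, death, intolerable toxicity".

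**Follow-up.** Section 3.1 also says: "For those whose condition is stable or improved after treatment, progression-free survival (PFS) follow-up will be carried out 8 weeks after the last administration". Section 6.4 repeats this every 12 weeks for stable or improving patients. Section 3.5 follows all patients, whatever their disease status, every 12 weeks for up to 3 years. Schedule note 17 continues imaging in patients who stopped drug for a reason other than progression.

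**Progression.** Section 5.12 item 2 makes progression a reason to stop, but adds that "subjects who meet the criteria for medication after disease progression can continue to be treated until the radiological evaluation confirms the progression".

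**Scans.** Section 7.2: "radiological examination will be performed to evaluate the tumor condition every 6 weeks (-7 days) until the completion of 6 cycles of treatment".

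**The concern.** Whether an SD patient stays on drug is an instruction to sites, and an analysis plan cannot repair it afterwards. A site working from 5.1.2 would stop drug in a patient with SD, possibly at the first scan. A site working from the phase II paragraph of 3.3 could continue to progression. Both would be following the protocol.

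Three things are at stake.

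- **Primary endpoint.** ORR is a best overall response. Stopping drug at the first SD scan could prevent a CR or PR that continued treatment would have produced.
- **PFS and OS.** Section 10.2 censors patients without progression or death at the last tumour evaluation for PFS, and at the last known survival date for OS. If a site takes the sentence to mean leaving the study, an SD patient is censored at that point. If another site follows 6.4, the same patient is observed to progression.
- **Consistency across centres.** The trial is multicentre, and the phase II decision rests on 7 and then 28 patients, so unequal handling of a few patients matters.

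**Working it through.** The point is textual. The plan's own design figure is reproduced first, only to show what the response count decides.

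**1. The design (section 10.1).** Inputs: p0 = 0.55, p1 = 0.80, boundaries 4/7 and 19/28. The trial continues with at least 5 of 7 responses and succeeds with at least 20 of 28.

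P(success | p) = Σ over x = 5, 6, 7 of P(X1 = x; 7, p) × P(X2 ≥ 20 − x; 21, p)

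- At p = 0.55: 0.043, within the one-sided 5%.
- At p = 0.80: 0.803, above the 80% required.

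The design reproduces and is not in dispute.

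**2. The phase II SD rule, section by section.**

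| Place | SD patient in phase II | Trigger scan | Role afterwards |
|---|---|---|---|
| 5.1.2 note | Withdrawn | None named | Out of the study, if literal |
| 3.3, phase Ib paragraph | Not addressed (phase Ib only) | None named | Not applicable |
| 3.3, phase II paragraph | No SD stop; can be read as continue to progression | None | Not stated |
| 3.1 | As in the 3.3 phase II paragraph | None | Stable patients off drug: PFS follow-up |
| 3.5 | Not addressed | None | All patients followed, up to 3 years |
| 6.4 | Not addressed | None | Stable patients off drug: imaging every 12 weeks |
| Schedule note 17 | Not addressed | None | Imaging continues unless drug was stopped for progression |

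Row 1 against rows 3 and 4 is the conflict on drug. Row 1 against the last four rows is the conflict on follow-up.

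**3. Earliest trigger.** Evaluation is every 2 cycles of 3 weeks: 2 × 3 = 6 weeks, window −7 days. Because 5.1.2 names no scan, a literal reader could act at week 6, or as early as week 5.

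**4. Can response come later than that?** For single-agent chidamide, section 1.1 reports 6 responders among 12 patients and says: "The median time to response was 5.9 (1.1 to 8.1) weeks". The longest time, 8.1 weeks, exceeds 6, so at least 1 of the 6 responded after week 6. The protocol does not say whether that patient was SD at week 6, and the combination may act faster. This shows that a late response is possible, not how often it happens.

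**5. Direction.** Removing a response from the count can never turn a failed trial into a successful one. P(success | p) also rises with p, so losing responses cannot lift the false-positive rate above 0.043. Any effect on ORR is downward.

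**6. The progression half of the sentence.** Section 5.1.2 withdraws PD patients without qualification. Section 5.12 item 2 allows some of them to continue until imaging confirms progression. This is a separate and smaller mismatch.

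**The case against.** The strongest reply is that only 5.1.2 expressly addresses SD in phase II, and it is explicit. Sections 3.1 and 3.3 never say that SD patients continue. The note in 5.1.2 uses a near-identical list of stopping events to limit treatment in responders, so the similar list in 3.1 and 3.3 may be the same sentence in looser English. SD withdrawal also appears three times across the two phases, which suggests that it is intended. This reading is possible, and it means that the sponsor, not the reviewer, should choose the rule. It does not remove the problem: on that reading 3.1 and 3.3 are silent on SD in phase II, 3.3 confines SD withdrawal to phase Ib, and no scan is named.

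A second reply is that the sentence sits in the treatment section, so withdrawal most naturally means stopping drug, and follow-up is provided for elsewhere. That is probably the intent. The words still say that the patient leaves the study.

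Several stronger readings are not supported:

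- **That 5.12 contradicts the SD rule.** Item 2 concerns progression only. The list omits SD as a reason to stop, but that is not an instruction to continue.
- **That patients with minor response (MR) are withdrawn too.** Appendix 2 makes MR (a decrease of 10% to under 30%) a separate category, and 5.1.2 names only SD and PD. What is missing is a positive statement for MR.
- **That a definite loss of power follows.** The protocol gives no share of responders who are still SD at week 6, and does not say whether the 0.80 target presumes treatment beyond SD. Any figure would rest on an invented fraction.
- **That responses after stopping drug are lost by rule.** Under note 17 scans continue, so they could still be recorded.

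**Conclusion.** The point stands as an inconsistency in the phase II instructions, with two main parts: whether and when SD ends treatment, and whether stopping treatment means leaving the study. The mismatch on progression with 5.12 item 2 is secondary. The consequence is possible under-recording of late responses and uneven PFS and OS censoring between sites. The effect on ORR is downward only and its size cannot be derived from the document; the false-positive rate is not raised. The ORR consequence assumes that at least one site acts on 5.1.2 at an early scan and that some patients with SD there would respond later on continued drug. It should be corrected, but it does not invalidate the design.

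**What to change.** 1. In 5.1.1, 5.1.2 and 3.3, replace withdrawal from the study with discontinuation of study treatment. State that patients off drug without progression continue the scheduled tumour assessments and that all patients continue survival follow-up.
2. State one phase II SD rule, identical in 3.1, 3.3 and 5.1.2. The choice is the sponsor's:
   - patients with SD or MR continue until progression, unacceptable toxicity or investigator decision; or
   - patients with SD stop at a named scan and patients with MR continue.
3. Make the progression wording in 5.1.2 agree with 5.12 item 2.

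The cost is wording in a few sections; the scans are already scheduled. The first option under item 2 adds some drug exposure in SD patients who will not benefit. The second accepts that some late responses may not be seen.

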**5.2. Packaging and storage of sintilimab**

The main active ingredient of sintilimab is a recombinant fully human anti-programmed death receptor 1 monoclonal antibody with a concentration of 10 mg/mL. This product is a clear, colorless liquid, free of foreign matter, flocculation and precipitation. Excipients include 140 mmol/L mannitol, 25 mmol/L histidine, 20 mmol/L sodium citrate dihydrate, 50 mmol/L sodium chloride, 0.02 mmol/L edetate disodium (ethylenediamine tetra Disodium acetate), 0.2 mg/mL polysorbate 80, pH 6.0.

The smallest packaging unit of sintilimab is a box, and each box contains one

Sintilimab injection packaged in a vial. The packaging box is printed with the name of the drug, dosage form, specification, drug code, production batch number, expiration date, storage conditions and information of the sponsor. The same information is printed on the label of the vial and the box, but there is no information of the dosage form, precautions, usage and dosage on the label of the vial. The labels of all packaging boxes and vials are marked with "For clinical research use only". Sintilimab products are stored in the dark at 2~8°C, and the validity period is 24 months. If there are quality problems such as turbidity and precipitation in the injection, it should be sealed up immediately and Innovent Company should be notified immediately.

The preparation and infusion process of sintilimab is as follows:

1. Draw out 2 bottles of sintilimab injection completely, add 100mL 0.9% (weight/volume) sodium chloride sterile saline intravenous infusion bag, and record the time of preparation start.
2. Gently invert the infusion bag to mix to ensure the uniformity of the medicine in the infusion bag and avoid foaming due to violent shaking. If a large amount of foam is generated, the drug should be allowed to stand until the foam disappears.
3. The drug is administered through an online filter equipped with 0.2~1.2μm (the infusion time is recommended to be controlled within 30-60 minutes), and the start and end time of the drug delivery are recorded.

**Note:**

- Before configuration, confirm that the sintilimab injection is transparent and there are no quality problems such as turbidity or precipitation;
- Ensure that the time from the first bottle of sintilimab injection to the end of administration does not exceed 24 hours (the storage of the prepared drug should be kept refrigerated at 2~8°C);

- Avoid mixing other drugs;
- Avoid intravenous bolus injection.

### 5.3 Toxicities of sintilimab

The safety summary data of Sintilimab came from 8 clinical studies conducted in China. A total of 1444 patients received at least one dose of Sintilimab, of whom 520 received Sintilimab monotherapy. Most patients received Sintilimab at a dose of 200 mg every 3 weeks. Among 520 patients who received Sintilimab monotherapy, the incidence of adverse reactions was 90.0%. Adverse reactions with an incidence  $\geq 10\%$  included: fever, thyroid function test abnormal, aspartate aminotransferase increased, alanine aminotransferase increased, proteinuria, rash, hypoalbuminemia, decreased appetite, hyperglycemia,  $\gamma$ -glutamyltransferase increased, blood bilirubin increased, lung infection, hypokalemia and neutropenia.

Grade 3 and above adverse reactions occurred in 28.7%, and 21% included pulmonary infection, anemia, pancreatitis, hypokalemia, hypertension, pneumonitis, increased  $\gamma$ -glutamyltransferase, decreased appetite, thrombocytopenia, neutropenia, increased aspartate aminotransferase, increased alanine aminotransferase, increased amylase, rash, abnormal liver function, and fever.

For more information, please refer to the drug manual.

### 5.4 Premedication of sintilimab

Among 2461 patients who had received sintilimab treatment, a total of 85 patients (3.5%) developed infusion reactions, including 40 patients (1.6%) with grade 1, 32 patients (13%) with grade 2, 11 patients (0.4%) with grade 3, and 2 patients (0.1%) with grade 4, and no grade 5 cases occurred. All were given observation or symptomatic care. Four patients (0.2%) permanently discontinued treatment, and 5 patients (0.2%) suspended the administration. The patient recovered.

The incidence of infusion reactions is low, pretreatment is not recommended. In exceptional cases, antihistamines may be administered to prevent infusion reactions.

